## Abstract

**Background:**

Evidence for interventions promoting oral health amongst care home residents is weak. The National Institute for Health and Care Excellence (NICE) guideline NG48 aims to maintain and improve the oral health of care home residents. A co-design process that worked with residents and care home staff to understand how the NG48 guideline could be best implemented in practice has been undertaken to refine a complex intervention. The aim of this study is to assess the feasibility of the intervention to inform a future larger scale definitive trial.

**Methods:**

This is a protocol for a pragmatic cluster randomised controlled trial with a 12-month follow-up that will be undertaken in 12 care homes across two sites (six in London, six in Northern Ireland). Care homes randomised to the intervention arm (n = 6) will receive the complex intervention based on the NG48 guideline, whilst care homes randomised to the control arm (n = 6) will continue with routine practice. The intervention will include a training package for care home staff to promote knowledge and skills in oral health promotion, the use of the Oral Health Assessment Tool on residents by trained care home staff, and a ‘support worker assisted’ daily tooth-brushing regime with toothpaste containing 1500 ppm fluoride. An average of ten residents, aged 65 years or over who have at least one natural tooth, will be recruited in each care home resulting in a recruited sample of 120 participants. Assessments will be undertaken at baseline, 6 months and 12 months, and will include a dental examination and questionnaires on general health and oral health administered by a research assistant. A parallel process evaluation involving semi-structured interviews will be undertaken to explore how the intervention could be embedded in standard practice. Rates of recruitment and retention, and intervention fidelity will also be recorded. A cost-consequence model will determine the relevance of different outcome measures in the decision-making context.

**Discussion:**

The study will provide valuable information for trialists, policymakers, clinicians and care home staff on the feasibility and associated costs of oral health promotion in UK care homes.

**Trial registration:**

ISRCTN10276613. Registered on 17th April 2020. http://www.isrctn.com/ISRCTN10276613.

## Introduction

### Background and rationale

Poor oral health is an increasingly common problem for older adults (defined as those over 65 years of age). According to the 2009 Adult Dental Health Survey undertaken in England, Wales and Northern Ireland, approximately 40% of the 75-84 age group and 33% of the 85+ age group had dental caries, whilst periodontal disease affected 69% of those over 65 years of age [1]. Oral conditions impact on the quality of life of older adults [2, 3] and their general health and diet [4, 5]. Access to domiciliary services is difficult, particularly for care home residents and hospital admission for dental problems can be distressing and costly [6, 7]. Income-related inequality in oral health of older adults is a major issue [8, 9]; therefore, effective prevention of oral diseases is paramount.

Approximately 400,000 older people live in care homes in the UK [10]. A care home is a broad term that refers to both residential and nursing care homes. About half of all care home residents have their own natural teeth [11] but their oral health is much worse than their peers living in the community (e.g. caries prevalence was 73% vs. 40%) [12]. Good daily oral hygiene is essential for oral health and the maintenance of complex dental restorations that are common amongst older adults. With increasing age, the ability to care for oral health (including dental restorations) can deteriorate and poly-pharmacy can lead to dry mouth [13]. Furthermore, diets can become rich in sugars [13]; especially in those who have a diminished appetite and rely on sugar to improve taste as well as provide additional calories to manage or prevent malnutrition and frailty. All these factors increase the risk of oral disease and directly impact on comorbidities, which in turn can worsen oral health.

Strategies for this population aim to prevent disease and to reduce pain and co-morbidity [14]. However, a Public Health England (PHE) survey showed oral healthcare provision and service in care homes to be poor [15]. A Priority Setting Partnership (PSP) exercise undertaken with four stakeholder groups, including service users, carers, third sector organisations and specialists such as those with specialist knowledge in Dental Public Health, Dental Health Commissioners and Geriatricians, found that maintaining function, dignity and the fear of losing the ability to look after their own teeth were key issues amongst older adults [16]. The World Health Organisation has focused on healthy ageing and prioritised the design of health and long-term care systems that are fit for ageing populations [17]. However, the evidence for interventions on promoting oral health amongst care home residents is weak [18]; no relevant systematic reviews have been published to date. There is uncertainty about effect size estimates, recruitment and retention of participants, intervention fidelity and appropriate outcome measures. This makes the design of a full trial problematic at this stage.

The National Institute for Health and Care Excellence (NICE) issued guideline NG48 [19], which aims to maintain and improve the oral health of care home residents. The aim of this multi-centre cluster randomised controlled trial (RCT) is to determine the feasibility of a complex intervention based on the NICE guideline for the oral health of older people in care homes. A parallel process evaluation will also be conducted, and a cost-consequence model developed to help plan for a definitive trial.

### Objectives

Determine the feasibility of undertaking a definitive trial to evaluate the complex intervention to promote oral health. To determine the following:
Proportion of care homes that agree to participate;Number of residents that are eligible and able to consent;Proportion of eligible residents that agree to participate;Proportion of participating residents that receive the intervention per the protocol;Proportion of care homes and residents that remain in the study;Proportion of completed measures used in the study (at least 75% completion rate required): (i) oral health assessments, (ii) quality of life questionnaires, (iii) clinical measurement records, (iv) oral symptoms checklist diaries; andImpact on recruitment of varying the 6-Cognitive Impairment Tool (6-CIT) [20] screening tool threshold.Undertake a parallel process evaluation to explore how the intervention could be embedded in standard practice guided by Pfadenhauer et al.’s framework [21] to maximise pathways to impact. Semi-structured interviews will be conducted with the following:Managers and staff to assess the intervention’s feasibility and sustainability;Residents to explore the intervention’s acceptability; andManagers and residents that refused participation to explore their reasoning.3.Develop a cost-consequence model to determine the relevance and relative importance of the different outcome measures in the decision-making context.

### Trial design

This is a pragmatic feasibility study to determine the feasibility of a multi-centre cluster randomised controlled trial of a complex intervention based on a recent NICE guideline for the oral health of older people in care homes [19]. Figure 1 provides an overview of the feasibility study’s design.

**Fig. 1 Fig1:**
[figure not shown]
Flowchart of recruitment, allocation, consent, intervention and analysis

## Methods: Participants, interventions and outcomes

### Study setting

This feasibility study will be undertaken in approximately 12 privately owned care homes across two sites (North London and Northern Ireland) with recruitment on both arms of the study in each site. Further information about recruitment and randomisation is presented in the relevant sections below.

### Eligibility criteria

Care homes (cluster level) will be eligible to participate if they have a minimum of 20 residents (as approximately half are expected to be edentate). They will not be eligible to participate if they only have high-dependency units or provide end-of-life care.

Care home residents (individual level) will be eligible to participate if they meet the following inclusion criteria and have the capacity to provide consent:
Aged 65 years and overDentate or partially dentateFull-time resident in care home

Care home residents will not be eligible to participate if they:
Are receiving end-of-life or palliative careHave severe cognitive impairment (6-CIT score of 10 or higher)Are currently taking part in another oral health intervention studyDo not have a working level of oral English

### Who will take informed consent?

For the two eligibility tests (6-CIT and brief dental check), written informed consent will be obtained from care home residents by a research assistant. For the feasibility study, written informed consent will be obtained from eligible care home residents by a research assistant or dental examiner. A research assistant will also take written informed consent for the interviews undertaken as part of the process evaluation and cost-consequence model. Written informed consent will be taken at least 48 hours after informing the participants about the study.

### Additional consent provisions for collection and use of participant data and biological specimens

Not applicable as no biological specimens will be collected as part of this trial.

## Interventions

### Explanation for the choice of comparators

Participants on the control arm will receive routine practice. The results from a PHE survey [15] and a PSP on the oral health of older adults [16] suggest that this practice is likely to be heterogeneous and include intermittent tooth brushing with toothpaste by the residents, who usually rely on support from the care home staff for their oral hygiene. This has been confirmed by a review of existing literature on oral health practices in care homes [22], as well as preliminary qualitative research findings from a recent project carried out in care homes in North London (unpublished). The process evaluation will enable the research team to gather information about current practice in care homes assigned to the control arm. Furthermore, collecting information on the control group’s willingness to be randomised to the control arm, as well as follow-up and response rates will help inform and plan for a future larger scale definitive trial.

### Intervention description

The description of the intervention below has been reported in accordance with the TIDieR (Template for Intervention Description and Replication) guidelines [23]. The intervention group will receive a complex intervention that fits within the Medical Research Council framework [24, 25] and is based on the recommendations of the NICE guideline (NG48) on ‘Oral health for adults in care homes’ [19]. The aim of the NG48 guideline is to maintain and improve the oral health of adults in care homes and ensure their timely access to dental treatment. The NG48 guideline is provided for the use of care home managers and care staff providing daily personal care to residents, community dental services and others. The guideline includes seven recommendations that cover oral health, including dental health and daily mouth care. The complex intervention will focus on three key recommendations that relate to the improvement of oral health without focusing on the provision of dental treatment: (1) care staff knowledge and skills, (2) oral health assessment and mouth care plans and (3) daily mouth care.

Intervention materials (Oral Health Assessment Tool (OHAT) [26], ‘Personal Oral Care Plan’, ‘Tips and tricks’ and ‘Weekly Oral Hygiene Record’) have been developed using a co-design process that worked with residents and care home staff to understand how the NG48 guideline could be best implemented in practice (method not described in this paper). This ensured that the materials were grounded in the experience of the older persons residing in care homes and those that provide their care. The aforementioned intervention materials are also supported by a care home staff training video to create a package of NG48-informed measures to promote knowledge and skills in oral health promotion, amongst care home staff. The training package had again been tested and refined by working with care home staff to promote fidelity. To further facilitate training and compliance, a dedicated web platform will be made available.

This complex intervention will include the following:
A care home staff training package (containing a training video and hard copy training manuals and laminated reference guides, as well as online training through a dedicated website as described above) to facilitate appropriate knowledge and skills to implement oral health promotion activities. Care home staff will be required to undertake formal training to support the residents’ oral health prior to the residents completing the baseline assessments. The training will be overseen by the care home manager and the research team, and will be added to the log of mandatory training. Following the initial training prior to baseline assessments, care home staff will have access to the training package online at anytime during the study. The turnover rate of employed staff working in the UK care sector is high; it is therefore probable that a change in care staff involved in the study will occur. As a result of this, the training package will also be part of the induction training for new staff members.Administration by trained care home staff of OHAT, a brief and practical assessment of the resident’s oral health needs that is reviewed and updated over time. Administration will take place immediately prior to the initial dental assessment at baseline and at the 12-month follow-up visit. Care home staff will also be asked to complete a ‘Personal Oral Care Plan’ for each resident following completion of the OHAT, and will be asked to update it after reassessment of the OHAT or after any dental visit.A ‘support worker assisted’ daily tooth-brushing regime with toothpaste containing 1500 ppm fluoride (provided by the study). This will involve care home staff brushing the teeth of residents who have problems with their oral self-care or providing assistance to those residents who are able to brush their own teeth. This may include reminders to brush their teeth as well as guidance on brushing appropriately. Tooth brushing will be undertaken twice daily, once in the morning and once in the evening. To facilitate this, a guide on how to deliver oral care will be provided in the form of a poster and ‘Tips and Tricks’ cards. These ‘Tips and Tricks’ cards are relevant to residents who can brush their own teeth, who require assistance or who might refuse care. Care home staff will be asked to record daily tooth brushing on the ‘Weekly Oral Hygiene Record’ along with any ‘Tips or Tricks’ they used. The record will be used to assess fidelity of the intervention implementation.

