Data will be collected to facilitate the assessment of the fidelity of the intervention. This refers only to the care homes in the intervention arm of the study and will include information on completion rates (fully, partially or not completed) for the following: (1) OHAT administered by trained care staff to participants; (2) Personal Care Plan for participants; (3) Weekly Oral Hygiene Record of participants; (4) Care Staff Completed Training.

As part of the process evaluation, semi-structured interviews with care home staff (managers, carers and other staff) and residents will assess the intervention’s feasibility (issues relating to recruitment, retention and fidelity) and acceptability. How the intervention could be embedded in standard practice will also be explored using the different domains of Pfadenhauer et al.’s [21] framework (Table 1). Specifically, the framework will be used to determine the factors that are important for implementation.

**Table 1 Tab1:** Domains and questions for reflection from Pfadenhauer et al. [21]

Main	Questions for reflection
Intervention characteristics	Which intervention characteristics interact with the setting, the context and the implementation? How do these intervention characteristics interact with the setting, the context and the implementation?
Context	How do aspects of the context interact with the intervention? Which aspects of the context interact with the implementation of the intervention?
Implementation theory	Which theoretical underpinning guides the implementation? How does this theory interact with the setting and the context? How does it interact with the intervention?
Implementation process	Which stages of the implementation process are passed through during implementation? How does the implementation process interact with the setting and the context? How does it interact with the intervention?
Implementation strategy	Which strategies are employed during implementation? How do these implementation strategies interact with the setting and the context? How do they interact with the intervention?
Implementation agents	Which agents are involved in the implementation effort? How do these implementation agents interact with the setting and context? How do they interact with the intervention?
Implementation outcomes	Which implementation outcomes are reported with the setting and the context? How do these implementation outcomes interact with the intervention outcomes?

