### Participant timeline

Figure 2 provides an overview of the feasibility study time schedule. At the allocation time point (t_−2_), recruited care homes will be randomly allocated to an intervention or control arm. At the enrollment time point (t_−1_), residents within the recruited care homes who are interested in taking part in the study will be asked to provide written consent to undergo two tests to determine their eligibility. If eligible, they will then be asked to provide informed written consent to take part in the feasibility study. The care homes allocated to the intervention arm will be asked to implement the oral health intervention based on the NICE guideline NG48 from baseline (t_0_) to the 12-month time point (t_2_), and the care homes allocated to the control arm will be asked to continue with their usual routine practice during the same 12-month period. Assessments (intervention and control group) will be undertaken at baseline (t_0_), 6 months after baseline (t_1_) and 12 months after baseline (t_2_). All assessments will take place at the care homes. More detailed information about the above processes is provided in the relevant sections below.

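### In intervention homes only, staff are trained and give the OHAT before the baseline examination, so some baseline measures are at risk of partial early exposure

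*Protocol article*

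**What the plan says.** All references are to the protocol article.

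- **Order of events.** Under Participant timeline, at the first time point "recruited care homes will be randomly allocated to an intervention or control arm". Residents are enrolled next, and baseline (t0) follows.
- **Training.** Intervention description requires formal staff training "prior to the residents completing the baseline assessments. The training will be overseen by the care home manager and the research team". It repeats the order: "Following the initial training prior to baseline assessments, care home staff will have access to the training package online at anytime during the study".
- **Staff OHAT.** The same section says of the OHAT given by trained staff: "Administration will take place immediately prior to the initial dental assessment at baseline and at the 12-month follow-up visit".
- **Both are parts of the intervention.** Its three components are listed as ("1) care staff knowledge and skills, (2) oral health assessment and mouth care plans and (3) daily mouth care").
- **One arm only.** Fidelity data cover staff training and the staff OHAT, and Outcomes says of them: "This refers only to the care homes in the intervention arm of the study". For the comparator, Participant timeline says that homes in "the control arm will be asked to continue with their usual routine practice during the same 12-month period".
- **Start of delivery.** Participant timeline says that intervention homes "will be asked to implement the oral health intervention based on the NICE guideline NG48 from baseline" (t0) to 12 months.

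The article does not state how long before baseline the training may take place. It does not ask staff to hold back new practice until the baseline examination is done.

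**The concern.** A baseline measurement should describe residents before either arm has received anything. Here one arm has had staff trained, and an oral assessment carried out by those staff, before the dental examiner arrives. Explanation for the choice of comparators notes that residents usually rely on staff for oral hygiene, so newly trained staff could alter mouth care before baseline.

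Two things are at stake. First, Outcomes says the study will supply estimates of treatment effects and help choose the primary outcome of the definitive trial, and Statistical methods says the sensitivity of the outcome measures will be explored. A baseline that has already moved in one arm makes a measure look less responsive than it is, most of all for measures that respond quickly. Second, Who will be blinded states that dental examiners are blind to allocation. A staff OHAT done in one arm only, directly before the examination, gives the examiner a chance to learn the arm.

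**Working it through.** **1. Is there an interval in which exposure could occur?** Allocation comes before enrolment. Recruitment then sets two consent steps, each at least 48 hours after information is given. A resident first approached after allocation therefore reaches baseline at least 2 × 48 = 96 hours later. The COVID-19 section allows face-to-face visits only in homes free of COVID for at least 14 days, so a baseline visit could slip after training is complete. Training may fall anywhere between allocation and baseline. The interval could be negligible or could run to weeks; the article does not say.

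**2. Which components come before the baseline examination?**

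| Component | Timing in the article | Could it move baseline values? |
|---|---|---|
| Staff training | Before baseline assessments | Yes, if staff change mouth care in the interval |
| Staff OHAT | Immediately before the dental examination | Not plausibly for plaque or bleeding; it is a risk to examiner blinding |
| Personal Oral Care Plan | After the staff OHAT | No earlier than the OHAT |
| Assisted brushing with study toothpaste | Not stated to start before t0 | Not on the text as written |

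Exposure is therefore partial at most, and training is its route.

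**3. Which measures are at risk?** Plaque, bleeding and the examiner-rated OHAT can respond to a short change in mouth care; symptoms and OIDP possibly can. Tooth count and caries are unlikely to change in such a time.

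**4. How much could it matter?** The article gives no figure on this point, so there is none to reproduce and the following is an illustration. Let Δ be the true 12-month difference between arms and f the share of it already present in the intervention arm at baseline. Let ρ be the correlation between baseline and 12-month values, with equal SDs at the two times.

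- 12-month values alone: the contrast is Δ. Nothing is lost.
- Change from baseline: Δ − fΔ = (1 − f)Δ.
- Baseline-adjusted: about Δ − ρfΔ = (1 − ρf)Δ.

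Share of Δ recovered, with f and ρ assumed:

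| f | Change score | Adjusted, ρ = 0.3 | Adjusted, ρ = 0.5 | Adjusted, ρ = 0.7 |
|---|---|---|---|---|
| 0 | 1.00 | 1.00 | 1.00 | 1.00 |
| 0.10 | 0.90 | 0.97 | 0.95 | 0.93 |
| 0.25 | 0.75 | 0.925 | 0.875 | 0.825 |
| 0.50 | 0.50 | 0.85 | 0.75 | 0.65 |

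If the definitive trial were sized on a change-score effect taken from this study, its sample size would be multiplied by 1/(1 − f)²: 1/0.81 = 1.23, 1/0.5625 = 1.78 and 1/0.25 = 4.0 for f = 0.10, 0.25 and 0.50.

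**5. What is untouched?** Recruitment, retention and completion proportions do not use baseline outcome values. The article's one precision figure, ±7% for 20% attrition in 120 residents, is of this kind: 1.96 × √(0.2 × 0.8 / 120) = 0.0716. It does not depend on the order discussed here.

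**The case against.** The strongest reply is that staff must be trained before they can deliver anything from t0, so preparatory training followed by delivery from baseline is a natural reading of both sections. That stands. A reader might infer a flat contradiction between Intervention description and Participant timeline, but the training can be reconciled with a t0 start. What needs clarifying is when delivery begins relative to the baseline measurements.

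A reader might also infer that every baseline value in the intervention homes is already a post-intervention value. The text does not support this. The component that acts directly on plaque and bleeding is the assisted brushing, which is not said to begin before t0. An OHAT done minutes earlier cannot change either measure. What remains is possible spill-over from training: a risk, not a demonstrated bias.

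Nor do the documents support a particular size. They give neither a pre-baseline improvement nor a true effect, and any honest range for f starts at 0. Losing most or all of the effect would require training alone to achieve it before the brushing regime starts. A distortion of the SDs does not follow either: a modest shift in one arm's mean need not materially change the within-arm spread.

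Finally, Statistical methods names neither a change score nor a baseline-adjusted model, only summaries and confidence intervals for differences between arms. Whether baseline values are used is left to the analysis plan, which is not shown. The loss in the table is therefore conditional on that choice.

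The order of events itself survives all of this. It is explicit, it is stated twice for training, it applies to one arm only, and it cannot be repaired once baseline data are collected.

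**Conclusion.** The point holds as a one-arm risk to baseline values and to baseline examiner blinding. It rests on three facts in the article (training and the first staff OHAT before the baseline examination, intervention homes only, after allocation is known) and one gap (no limit on the training-to-baseline interval). The further step, that staff change mouth care in that interval, is plausible but not established.

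The size is unknown and may be nil. The attenuation in the table applies only if f exceeds 0 and the analysis uses baseline values. With no primary outcome and a descriptive analysis, no confirmatory result is at stake. The harm is confined to the interpretation of baseline and to change-based or baseline-adjusted estimates carried into the definitive trial. This is a cheap improvement worth making before recruitment begins, which Trial status says has been postponed. It is not a critical defect.

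**What to change.** In every home, complete the baseline dental examination, examiner OHAT, OIDP, EQ-5D-5L and baseline symptom checklist before staff training and the first staff OHAT begin there. Amend both statements on training and the one on the staff OHAT in Intervention description, and reconcile them with Participant timeline on when delivery starts relative to t0. Suggested wording:

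*Baseline outcome measurements are finished in each home before staff training or staff use of the OHAT starts in that home. Where this is not possible, the dates of training and of each resident's baseline assessment are recorded and the interval is reported.*

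The cost is a change in visit order, a short text amendment, and a brief gap between baseline measurement and the start of delivery in intervention homes.

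Moving baseline ahead of allocation is not proposed. It would put screening, two consents and a dental visit before randomisation and would redesign the sequence in Participant timeline and Sequence generation. Because residents would still be enrolled after allocation, the re-ordering does not make every baseline difference attributable to chance; it removes only the part that early training could cause. It also leaves in place the staff OHAT at the 12-month visit, whose order relative to the blinded examination should be considered when the text is amended.
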